### **16.5 Criteria for the termination of the trial**

Any new evidence from previous or current studies that Losmapimod may have serious detrimental effects in the trial population, in the opinion of the CI, the trial will be discontinued. Another criterion will be failure to recruit sufficient participants to complete, in the opinion of the CI, analysis of the data collected.

### **16.6 Procedure to account for missing or spurious data**

The primary analyses will be performed on the pharmacodynamic population. Formal regression analysis will be based on the subset of participants who have all data points observed: complete cases. This assumes that the reason for any missing data is independent and unrelated to the data values, either observed or unobserved. The level of missing data will be documented and sensitivity analysis considered if the incidence of missing data in the primary endpoint is greater than 20%.

All summary statistics will report both the population size and the number of non-missing observations. Summary statistics will ignore any missing data and thus make the same assumptions as described above.

### **16.7 Definition of the end of the trial**

The end of trial definition will be 3 months after last participant last visit.

## **17 Data handling and record keeping**

### **17.1 eCRF**

All data will be transferred into a electronic Case Report Form (eCRF) which will be anonymised. All trial data in the eCRF must be extracted from and be consistent with the relevant source documents. The eCRFs must be completed, dated and signed by the investigator or designee in a timely manner. It remains the responsibility of the investigator for the timing, completeness and accuracy of the eCRF pages. The eCRF will be accessible to trial coordinators, data managers and the investigators as required.

The investigator will also supply the trial coordinator with any required, additional, background information from the medical records as required.

The investigators must ensure that the eCRFs and other trial related documentation is sent to the trial coordinator containing no participant identifiable data.

### **17.2 Source Data**

To enable peer review, monitoring, audit and/or inspection the investigator must agree to keep records of all enrolled participants (sufficient information to link records e.g., CRFs, hospital records and samples), all original signed informed consent forms and copies of the CRF pages.

Source data includes but is not limited to:

- Informed Consent Form
- Medical Records
- ECG Print outs
- Scan images
- On-line test results systems
- Prescriptions

### **17.3 Data Protection**

All investigators and trial site staff involved in this trial must comply with the requirements of the Data Protection Act 1998 and Trust Policy with regards to the collection, storage, processing and disclosure of personal information and will uphold the Act's core principles.

## **18 Trial Steering and Data Monitoring Committee**

The Trial Steering Committee (TSC) is responsible for the day to day running of the trial and related activities. The composition of the TSC is stated on page 3 of the protocol. The TSC also provides overall supervision for the trial, to ensure that it is conducted in accordance with the protocol and GCP and to provide advice through its independent chairman ([name], [contact]). The committee will aim to convene at regular intervals to review the data and discuss if the trial is on course to meet the sample size requirements. The committee will appoint a DMC and a DMC charter will be prepared prior to any DMC meetings including an interim analysis plan, although this may evolve over the course of the

trial. The DMC will be composed of persons not involved in the direct running, management or final analysis of the trial. The DMC will examine the recruitment rates, safety profile, and efficacy and mechanistic endpoints. The time scale and funding of the trial is limited and the ability of the trial to deliver data of sufficient scientific value will be considered. Adaptations to the trial may include but are not limited to:

- Revisions to the sample size, including early trial cessation
- Revisions to the randomisation ratio to reflect different variability of the primary endpoint in the treatment groups

The DMC will provide recommendations to the TSC. The TSC will retain ultimate responsibility to choose whether or not to follow the recommendation of the DMC.

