### **11.9 Treatment Assignment**

Participants will be randomised to the Losmapimod or Placebo regimen in a 1:1 ratio. The randomisation will be stratified by treatment centre. A delegated member of the trial team will log into the website <https://prod.tenalea.net/cctu/DM/default.aspx> using a secure password. They will enter the following information

- Subject Number
- Subject Initials
- Subject DoB
- Confirmation of eligibility
- Inc/Exclusion criteria confirmation

The system will provide a box number which will be used by the site pharmacy to provide the treatment allocated in a double-blinded manner.

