Formal ANCOVA analysis will be performed on the change from baseline, with fixed effects for the treatment and adjustment for baseline value and treatment centre. Estimates of the treatment effect, (Losmapimod – Placebo) will be provided with 95% confidence intervals and p-values. All estimated regression parameters will be reported in a similar fashion. Comparisons of proportions will be handled using a similar approach based on logistic regression to estimate odd ratios.

As an exploratory trial the focus will be estimation and interpretation of treatment effects and not on formal hypothesis tests. As such no adjustment for the extensive multiple testing will be done.

Secondary endpoints will have similar summary measures reported broken down by time-point and treatment group. Endpoints that are repeatedly observed in the intermediate visits during treatment will be summarised graphically. Regression analysis may be performed.

A detailed statistical analysis plan will be finalised prior to data base lock, although it is anticipated that this will be the first stage in reporting and subsequent post-hoc analyses will be performed and documented as being post-hoc.

Figure 1 illustrates some of these derived variables.

[figure not shown]

Figure 1: Stylised diagram of an artery to demonstrate the various PET indices that are derived from the regions of interest (ROI) placed on the vessel. A circular ROI is drawn to encompass the vessel wall on each contiguous axial segment. Each axial segment then provides two numbers: a mean and a maximal value for the FDG uptake within that segment, expressed as the TBR. The MeanMean TBR is the averaged Mean TBR values from each artery. The MeanMax TBR is the averaged Max TBR values from each artery. The most diseased segment (MDS) is centred on the darkest red segment, defined as having the highest maximal TBR value in the entire artery. When averaged with the segments immediately above and below it, these three segments yield the MDS. Example values and their derivations are provided in the lowest row

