### **16.4 Number of Participants to be enrolled**

A sufficient number of participants will be enrolled so that approximately 60 participants who fulfil the primary statistical analysis population as described in Section 16.2 (approximately 30 participants per arm) complete the trial. Sample size is based in part on feasibility.

As an exploratory trial a formal power calculation is inappropriate. The analysis will focus on estimating the differences between treatments and will provide 95% confidence intervals of the form  $x \pm y$ , where  $x$  is the estimate and  $y$  is the confidence interval half-width. A smaller value of the half-width is desirable as it gives greater precision to the trial's conclusions. The value of the half-width depends, on the SD of the endpoint under consideration, the number of participants and an element of chance variation.

Based on the results of a previous GSK trial, PM1111138 "A double-blind, placebo-controlled, parallel group trial to evaluate the effects of two regimens of GW856553, over a period of 3 month, on in-vivo macrophage activity, as assessed by FDG-PET/CT imaging, in the carotid arteries and aorta of patients with established atherosclerosis" a SD of around 0.3 is estimated in many of the endpoints on the TBR scale that were considered. Under this assumption, with 30 participants per arm, there is a chance of 90% of achieving a half-width of 0.17 or less.

Such precision will be meaningful for drawing conclusion. Moreover a sample size of 30 participants per arm will provide enough data to be able to check assumptions behind the statistical analyses.

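### If the randomisation ratio is revised because the arms differ in variability (section 18), an ordinary pooled-variance ANCOVA (section 16.1) reports intervals that are too wide and hides the precision gained

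*Protocol*

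**What the plan says.** Section 11.9 sets the allocation: "Participants will be randomised to the Losmapimod or Placebo regimen in a 1:1 ratio", stratified by centre. Section 18 lets the DMC recommend adaptations to the TSC, and one of the two listed is "Revisions to the randomisation ratio to reflect different variability of the primary endpoint in the treatment groups". It gives no direction, trigger or timing for the change.

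Section 16.1 fixes the analysis: "Formal ANCOVA analysis will be performed on the change from baseline, with fixed effects for the treatment", adjusted for baseline value and centre. The treatment effects "will be provided with 95% confidence intervals and p-values". Nothing is said about the residual variance by arm.

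Section 16.4 plans with one SD for both arms ("a SD of around 0.3 is estimated in many of the endpoints on the TBR scale that were considered") and measures precision by the half-width of the confidence interval: "A smaller value of the half-width is desirable as it gives greater precision to the trial's conclusions". The target is that "with 30 participants per arm, there is a chance of 90% of achieving a half-width of 0.17 or less". No section connects a revised ratio to an analysis that allows unequal variances.

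**The concern.** The ratio would be revised only when the arms appear to have different variances. The revision that serves the stated purpose puts more participants in the more variable arm. An ordinary ANCOVA estimates one residual variance from all participants, so the larger, noisier arm dominates it. That variance is then applied to the smaller, quieter arm as well, and the standard error of the treatment difference is overstated.

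At 30/30 the same model gives essentially the right standard error even with unequal SDs. The mismatch therefore arises only when the adaptation is used. What is at stake is the quantity by which section 16.4 justifies the sample size: the reported half-width would get worse under a change made to improve it.

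**Working it through.** **1. The plan's own figure.** Inputs from section 16.4: SD 0.3, 30 per arm, 95% interval. Half-width = crit × s × √(2/30), with s² distributed as 0.09 × χ²(58)/58.
- With crit = 1.96, the expected-scale half-width is 1.96 × 0.3 × √(2/30) = 0.152, and P(half-width ≤ 0.17) = 0.908.
- With t(58), the half-width is 0.155, P = 0.861, and the 90th percentile is 0.173, which rounds to 0.17.

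The stated 90% is therefore reproduced, to rounding.

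**2. Assumptions for the check.** N = 60 in total and the mean of the two arm variances held at 0.09. The SD ratio k (noisier over quieter arm) is not in the documents, so a range is used. Splits are written quieter/noisier.

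**3. Formulas.** Subscript 1 is the noisier arm.
- Pooled: s_p² = [(n₁−1)s₁² + (n₂−1)s₂²]/58; SE = s_p × √(1/n₁ + 1/n₂).
- True: SE = √(s₁²/n₁ + s₂²/n₂).
- With allocation proportional to SD, pooled variance over true variance of the difference is about k − 1 + 1/k. That is 1.05 at k = 1.25, 1.17 at k = 1.5 and 1.5 at k = 2.

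**4. Worked case, k = 2.** s₁² + s₂² = 0.18 and s₁² = 4s₂² give s₁² = 0.144 and s₂² = 0.036.
- 30/30: true and pooled SE are both √(0.18/30) = 0.0775; half-width 0.155.
- 25/35: s_p² = (34 × 0.144 + 24 × 0.036)/58 = 0.0993. Pooled SE 0.0825, half-width 0.165. True SE 0.0745, half-width 0.149.
- 20/40: s_p² = (39 × 0.144 + 19 × 0.036)/58 = 0.1086. Pooled SE 0.0903, half-width 0.181. True SE 0.0735, half-width 0.147.

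So the true SE falls by about 5% at 20/40 (0.0735 against 0.0775), while the reported half-width rises by about 16.5%.

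**5. Simulation of the ANCOVA** (treatment, baseline, centre; up to 20,000 replicates per cell; repeat runs agree to about one percentage point):

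| k | Split | Mean half-width, pooled | Mean half-width, HC2 | Null rejection, pooled | P(half-width ≤ 0.17), pooled |
|---|---|---|---|---|---|
| 1.5 | 30/30 | 0.157 | 0.157 | about 5% | 79% |
| 1.5 | 27/33 | 0.161 | 0.155 | 4.0–4.5% | 71% |
| 1.5 | 24/36 | 0.167 | 0.155 | 3.4–3.8% | 59% |
| 2 | 30/30 | 0.157 | 0.157 | about 5% | 77% |
| 2 | 25/35 | 0.167 | 0.152 | 3.3% | 57–58% |
| 2 | 22/38 | 0.176 | 0.151–0.152 | 2.2–2.4% | 38% |
| 2 | 20/40 | 0.183 | 0.152 | 1.7% | 25–26% |

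HC2 keeps null rejection at about 5% throughout. At k = 1.25 the SD-proportional split gives an analytic half-width of 0.158 against a correct 0.154, which is 2.5% too wide.

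**The case against.** Section 16.1 never states equal variances; that comes from reading ANCOVA in its ordinary form. The protocol announces a detailed SAP and a DMC charter with an interim analysis plan, and either could specify the variance estimator. Section 16.4 also expects assumptions to be checked. This stands as a limit: the protocol does not rule out a robust analysis. It does, however, name both the analysis and the adaptation, and the default form of the one works against the purpose of the other.

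The size is also limited by timing. The ratio can change only after some week-16 data have been seen, from a 1:1 start. If the change came at 15/15, a final 25/35 needs 10:20 afterwards, 20/40 needs 5:25, 17/43 needs 2:28, and 15/45 needs 0:30, which is no longer randomisation. A reader might infer from SD-proportional splits at SD ratios of 2.5 or 3 that power falls by 20 points or more. The documents do not support that: those splits are not realistic, the SD ratios have no source, and sections 16.1 and 16.4 set estimation, not power, as the criterion.

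Finally, the adaptation is optional. The DMC recommends, the TSC decides, and a departure from 1:1 would presumably need an amendment, in which analysis wording could be added. This lowers the priority but does not remove the point.

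**Conclusion.** The point holds in a conditional form. If the ratio is revised towards the more variable arm and the ANCOVA pools the variance, the reported 95% interval is conservative and wider than if 1:1 had been kept. At an SD ratio of 1.5 the mean half-width is 0.161 to 0.167, against 0.155 with HC2. At a ratio of 2 it is 0.167 to 0.183, against 0.152. A mean above 0.17 needs an SD ratio near 2 and a large shift in allocation; below a ratio of about 1.25 the effect is negligible. All of this assumes N = 60 and mean residual variance 0.09.

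A reader might infer that the trial itself loses precision or that its estimate is biased. Neither follows: the estimator stays unbiased and its true standard error falls slightly, and it is the reported interval that hides the gain. Nor does the point imply excess false positives. Intervals would be too narrow only if participants were moved to the quieter arm, which would defeat the stated purpose, although section 18 does not give the direction. Because the adaptation may never be used, this is an item to consider and not an essential correction.

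**What to change.** Add to section 16.1: if the randomisation ratio is revised, the ANCOVA will use arm-specific residual variances with Satterthwaite degrees of freedom, or HC2/HC3 standard errors, and will include a term for randomisation stage (before or after the change). The stage term is needed because, once the ratio changes, treatment is associated with time of entry, and any drift over time would otherwise enter the treatment comparison.

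The cost is one or two sentences, one model parameter and, if the variances turn out equal, a slightly less stable interval. At 30/30 the HC2 and pooled half-widths were the same in simulation (0.157). The option to revise the ratio need not be deleted; whether to keep it is a separate trade-off.

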### **12.1.2 Screening, V1 (Day -45 to Day -14)**

Participants will attend the unit for a screening visit within 45 days prior to administration of the first dose of trial medication (V3). Written informed consent must be obtained prior to performance of any protocol specific procedures. The following procedures will be performed:

- Medical history including smoking history.
- Current medication history prior to the screening visit.
- Demography (date of birth, age, gender and race).
- Physical examination including height, weight, BMI, vital signs.
- 12-lead ECG (triplicate).
- Spirometry post bronchodilator.
- Following an overnight fast, blood (approximately 55ml) and urine will be collected for clinical chemistry (including urea, creatinine, uric acid, electrolytes, liver function and glucose and HbA1c if diabetic), Full Blood Count (including haemoglobin, platelets and differential white cell count), HIV, Hepatitis B surface antigen, Hepatitis C antibody, urinalysis.
- Biomarkers.

Participants detailed cardiovascular and respiratory (and other systems) medical history will be collected, including information regarding any known allergies to drugs, use of concomitant medications, detailed history of smoking and alcohol consumption and history of blood donation and/or participation in clinical trials. The 45 day screening period may be extended if patients have an exacerbation that requires steroid or antibiotic use. This period will be extended by at least the equivalent time of steroid use added onto the 45 day period or up to the discretion of the PI where clinical judgement is required. Patients who have failed screening because of changes to trial inclusion/exclusion criteria or did not attend screening due to medical reasons (i.e. an exacerbation) and their medical status has now changed may be rescreened if they are keen to participate in the trial and happy to undergo a repeat screening, at the discretion of the PI and based on clinical judgement.

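### If the randomisation ratio is revised mid-trial, as Section 18 allows, the ANCOVA in Section 16.1 needs a factor for allocation period

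*Protocol*

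**What the plan says.** Section 11.9 of the protocol sets the allocation: "Participants will be randomised to the Losmapimod or Placebo regimen in a 1:1 ratio". It adds: "The randomisation will be stratified by treatment centre". No other stratification factor is named.

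Section 18 makes the ratio revisable. It introduces an open list with "Adaptations to the trial may include but are not limited to", and one item is "Revisions to the randomisation ratio to reflect different variability of the primary endpoint in the treatment groups". No trigger, size, timing or limit on the number of revisions is given. The interim plan is left to the DMC charter: "a DMC charter will be prepared prior to any DMC meetings including an interim analysis plan, although this may evolve over the course of the" (quotation cut at a page break).

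Section 16.1 specifies the analysis of change from baseline as an ANCOVA "with fixed effects for the treatment and adjustment for baseline value and treatment centre", with a similar logistic approach for proportions. It also says: "A detailed statistical analysis plan will be finalised prior to data base lock". Nothing in the protocol connects the analysis model to a change in the ratio.

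**The concern.** With a fixed ratio, randomisation balances calendar time between the arms in expectation. Once the ratio changes, that holds only within each allocation period. Pooled over periods, the arm favoured after the revision holds a larger share of late participants. A model without a period term then attributes part of any early-to-late difference in outcome to treatment. This is a bias in the estimate, and it is a different matter from the unequal variances that would prompt the revision.

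The protocol gives some reason to expect that conditions may not stay constant. Section 12.1.2 provides for rescreening of "Patients who have failed screening because of changes to trial inclusion/exclusion criteria". Section 16.1 calls the identification and tracking of inflamed tissue subjective and leaves the handling of the uptake data open to revision. Neither statement shows that the 16-week change drifts.

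What is at stake is the treatment estimate and its 95% interval, on which Sections 16.1 and 16.4 rest the trial's conclusions.

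**Working it through.** **Inputs from the protocol.** 60 participants, 30 per arm; SD 0.3 on the TBR scale; 95% intervals; half-width 0.17 (Section 16.4). Enrolment over about 24 weeks (Section 9.4). Post-treatment PET at Days 105 to 111 (Section 12.1.5, V8).

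**Assumptions, not in the documents.** A revised ratio of 1.5:1, 2:1 or 3:1; a single revision; drift in the change score, given baseline and centre, of 0.1 to 0.3 TBR (one third to one SD); even accrual.

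**1. The plan's own figure.** The expected half-width is 1.96 × 0.3 × √(2/30) = 0.152. Letting the sample variance vary as a chi-square on 58 degrees of freedom, the 90th percentile is 0.169 and P(half-width ≤ 0.17) = 90.8%. The stated 90% is reproduced. With the t quantile the 90th percentile is 0.173 and the probability 86.1%.

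**2. Share of the drift that becomes bias.** Without a period term,

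bias = drift × k, where k = (share of losmapimod participants in period 2) − (share of placebo participants in period 2).

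Expected numbers for a revision favouring losmapimod (favouring placebo reverses the sign):

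- Halfway, 2:1: k = 20/35 − 10/25 = 0.171.
- Halfway, 3:1: k = 22.5/37.5 − 7.5/22.5 = 0.267.
- After 50, 2:1: k = 6.67/31.67 − 3.33/28.33 = 0.093.
- After 50, 3:1: k = 7.5/32.5 − 2.5/27.5 = 0.140.

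For a revision anywhere between one third and two thirds of enrolment, k is 0.09 to 0.10 at 1.5:1, 0.15 to 0.17 at 2:1 and 0.23 to 0.27 at 3:1. With the ratio unchanged, k = 0.

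**3. Size of the bias.**

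| Revision | Ratio | k | Bias at drift 0.1 | Bias at drift 0.3 | % of 0.17 |
|---|---|---|---|---|---|
| After 50 of 60 | 2:1 | 0.093 | 0.009 | 0.028 | 5 to 16 |
| After 50 of 60 | 3:1 | 0.140 | 0.014 | 0.042 | 8 to 25 |
| After 30 of 60 | 2:1 | 0.171 | 0.017 | 0.051 | 10 to 30 |
| After 30 of 60 | 3:1 | 0.267 | 0.027 | 0.080 | 16 to 47 |

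**4. Which timing is feasible.** The stated reason for a revision is the observed variability of the primary endpoint. The PET endpoint is first available at Day 105, that is week 15. Even accrual is 60/24 = 2.5 per week.

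- The 30th participant is randomised at week 12, before anyone has a post-treatment scan.
- The 40th is randomised at week 16, when only those from the first week (2 or 3) can have one.
- The 50th is randomised at week 20, when those from the first five weeks (about 12) can have one.

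On the stated schedule only a late revision could be informed by PET variability. The halfway rows need enrolment to run well beyond 24 weeks.

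**5. Effect on the interval.** Simulated trials (20,000 per setting, 30 + 30 participants, residual SD 0.3, model with treatment, baseline and centre):

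| Setting, halfway revision | Bias, no period term | Coverage | Bias, period term | Coverage |
|---|---|---|---|---|
| 2:1, drift 0.15 | 0.027 | 94.6% | 0.000 | 95.0% |
| 2:1, drift 0.30 | 0.051 | 93.5% | 0.001 | 94.9% |
| 3:1, drift 0.30 | 0.075 | 89.6% | 0.000 | 94.8% |
| 2:1, drift 0.30 in baseline level only | −0.001 | 95.0% | 0.000 | 95.0% |

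The 3:1 bias is 0.075 rather than 0.080 because whole participants are allocated (22 and 8). Coverage falls less than the bias alone would suggest, because unmodelled drift also inflates the residual SD and widens the interval.

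**6. Price of the period term when there is no drift.** Over revisions between one third and two thirds of enrolment, the standard error rises by about 0.5% at 1.5:1, 1.3 to 1.5% at 2:1 (halfway 0.0786 to 0.0797) and 3.0 to 3.5% at 3:1 (halfway 0.0800 to 0.0828).

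**The case against.** The strongest reply is that this belongs in documents not shown here. A detailed SAP is promised before database lock, and the interim plan goes to the DMC charter. The model in Section 16.1 is correct for the 1:1 design in Section 11.9, and a new ratio would alter Section 11.9, so the amendment procedure in Section 19.4 offers a further occasion to update the model. It stands that the SAP could add the term. But the protocol itself names the covariates and itself permits the revision, and the two do not fit together as written. A term added only after a revision would also follow a DMC review that includes efficacy endpoints, and would look like a post-hoc choice of model.

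The second reply is about size, and most of it stands. The drift has no figure in the documents. Changing eligibility criteria are not evidence that the 16-week change drifts. The halfway scenario does not fit the stated enrolment period. If the ratio were set in proportion to the two SDs, which minimises the variance of the difference, 2:1 or 3:1 would need one arm's SD to be two or three times the other's, so a smaller shift is more likely.

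The third reply is that the trial is exploratory and makes no formal tests. That weakens any argument from type I error. It does not answer a bias in the estimate, since estimation is the stated purpose.

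**Conclusion.** The point holds conditionally. If the ratio is revised and the Section 16.1 model is used as written, part of any drift in the change score not explained by baseline and centre passes into the treatment effect. That part is about 0.09 (2:1) or 0.14 (3:1) for a revision after 50 of 60 participants. It is 0.15 to 0.17 or 0.23 to 0.27 for a revision between one third and two thirds of enrolment, if enrolment runs long enough to allow one. With an assumed drift of 0.1 to 0.3 TBR, the bias is about 0.01 to 0.04 for the late revision and 0.02 to 0.08 for the halfway one. Coverage drops materially, to about 90%, only when a 3:1 ratio and a drift of a full SD occur together.

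A reader might infer that any drift over calendar time biases this trial's treatment effect. The documents do not support that. The revision is optional, drift in baseline level is absorbed by the baseline covariate (given a linear relation), and differences between centres are absorbed by the centre term. Nor do they support taking the halfway figures as the expected size.

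This is a modest weakness in the stated model. It is worth correcting because the correction is nearly free.

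**What to change.** Add one sentence to Section 16.1 or Section 18: if the randomisation ratio is revised, the ANCOVA models also include a factor for allocation period (before and after each revision), so that the treatment effect is estimated within periods. The same should apply to the logistic models where event counts allow; that part was not simulated, and with about 60 participants sparse outcomes may not support the extra factor. The SAP should repeat the rule.

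The cost is one degree of freedom per revision (56 to 55 residual degrees of freedom for the first) and the 0.5 to 3.5% rise in standard error shown above when there is no drift. No new data are needed, because the period follows from the randomisation date. Nothing changes if the ratio stays at 1:1.
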